**Severe acute malnutrition**						
	**7%**					
		70	9.1	95	85.9
		70	11.7	90	78.3
		70	13.5	85	71.5
	**4%**					
		40	12.2	95	82.8
		40	15.6	90	74.4
		40	17.8	85	67.2

^a^Prospective observational study.

^b^Randomized controlled clinical trial evaluating the optimal duration of treatment with amoxicillin for fast breathing pneumonia.

^c^Alpha value set to 5% and power set to 80%.

^d^Randomized controlled clinical trial evaluating the optimal duration of treatment with amoxicillin for chest indrawing pneumonia.

^e^Assuming similar values for fast breathing pneumonia and chest indrawing pneumonia to be able to compare the ITIP1 and ITIP2 cohorts.

### Data Collection and Quality Assurance

All study data are collected by clinical study staff using designated source documents or paper-based case report forms (Multimedia Appendix 2), which are then entered into electronic databases. Clinical research data are maintained through a combination of a secure electronic data management system and physical files with restricted access to ensure confidentiality. Data related to the study endpoints will be extracted from the electronic databases for statistical analyses. Two distinct study databases are maintained: the primary study database with study visit data and a database with participating children’s personally identifiable information. The database with identifiable information is maintained separately by the study site, while the designated contract research organization (CRO) maintains the primary study database. To ensure accuracy and completeness, data are routinely reviewed by the site quality control and assurance team as well as the coinvestigators who monitor the site and perform quality assurance reviews, audits, and evaluation of the study safety and progress. Standard Good Clinical Practice (GCP) is followed to ensure accurate, reliable, and consistent data collection.

### Data Management

Primary data management activities, which include data entry and validation, data coding and cleaning, database quality control, disaster recovery plans, preparation and submission of compliance reports, and preparation of final study database, are undertaken by the designated CRO. The on-site study data manager oversees data-related procedures at the study site and is supervised by the CRO data management staff. Data management activities are performed using Clindex Clinical Trial and Data Management software, developed by Fortress Medical Systems (Hopkins, MN). All data management activities are in compliance with the International Council on Harmonization (ICH) GCP E6 (R2), a regulatory sponsoring organization, and institutional requirements for the protection of children and confidentiality of personal and health information.

### Outcomes

The primary endpoint is whether children treated for pneumonia are cured 14 days from diagnosis. Secondary endpoints are treatment regimens in ITIP3; treatment responses of children in ITIP3 in comparison to those in the standard care groups in ITIP1 and ITIP2 as measured by vital signs, oxygen saturation, laboratory test results, length of hospital stay; proportion of children who are rehospitalized or die; and proportion of children in ITIP3 who are clinically cured by day 14 (characteristics such as gender, age, weight, mid-upper arm circumference, HIV status, malaria, and vaccination status were considered).

### Statistical Analysis

Generalized linear models with robust standard error will be used to compare the percentages (absolute risk differences) of children who are clinically cured by day 14 among ITIP3 children who have severe malaria (or are anemic or present with severe acute malnutrition, or are HIV positive or exposed) and children in the standard care groups in ITIP1 or ITIP2. Two-sided tests will be performed, with an alpha value of 0.05. No adjustments will be made for multiple comparisons because of the observational and exploratory nature of this study. If loss to follow-up is higher than 5%, multiple imputations will be considered for sensitivity analyses. The imputations will be performed separately for each cohort using multiple (n=20) hot deck imputations and the child’s age and gender and educational status of the caregiver. Multiple imputation estimates will be combined using the approach by Rubin [8]. Similar linear or generalized linear models will be used for secondary outcome analyses. Where appropriate, we will adjust for gender, age, weight, mid-upper arm circumference, HIV status, malaria, and vaccination status.

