### Sample Size

The primary objectives of ITIP3 are to describe the clinical outcomes of children who meet the inclusion criteria for ITIP3 and to investigate whether the percentages of children cured on day 14 among those with either fast breathing or chest indrawing pneumonia and comorbidities such as severe malaria, anemia, severe acute malnutrition, or HIV are lower than those without these comorbidities in the standard of care groups in the concurrent clinical trials. For hypothesis testing, we focused on four high-frequency and high-mortality comorbidities (ie, severe malaria, anemia, severe acute malnutrition, and HIV infection or exposure) within ITIP3. We estimate that the study can enroll 1000 children during the time it is concurrently conducted with the ITIP1 and ITIP2 clinical trials, and we estimate the effect sizes for the primary outcome comparisons for which we have 80% power. We also assume that 1000 children can be enrolled in each of the standard care groups in ITIP1 and ITIP2. With available data from KCH and Malawi, we estimate the prevalence of severe pneumonia to be 10%-24%, severe malaria to be 15%-20%, severe acute malnutrition to be 4%-7%, and HIV seropositivity to be 5%-10%. Based on the estimated treatment failure rates for ITIP1 and ITIP2, we conservatively estimate that clinical cure will be observed in 90%-95% of children in ITIP1 and 85%-90% in ITIP2. We estimate the effect sizes we would be able to see for various comparisons between ITIP3 and ITIP1 or ITIP2, along with different estimated prevalence rates (Table 1). For example, comparing the clinical cure among children with HIV infection or exposure in ITIP3 and those in the standard of care group in ITIP2, if the prevalence of HIV infection or exposure is 10% in ITIP3, we will have 80% power to detect an absolute difference in proportions of 9.9% if at least 90% of the children in ITIP2 are cured and 80.1% of the children with HIV infection or exposure in ITIP3 are cured. Note that the absolute observable difference is largest for severe acute malnutrition, as that outcome is expected to have the lowest prevalence among the outcomes of interest. Nonetheless, we considered all the estimated effect sizes to be clinically relevant.

**Table 1 table1:** Observable effect sizes for comparisons of Innovative Treatments in Pneumonia (ITIP) 3^a^ with ITIP1^b^ or ITIP2^c,d^. N (ITIP1 or ITIP2) = 1000.

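### Table 1's 80% power fits a pooled two-proportion test; a robust Wald test of the unadjusted risk difference would have 52% to 75% power at the printed differences

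*Protocol article*

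**What the plan says.** The Sample Size section of the protocol article takes enrolment as given: "We estimate that the study can enroll 1000 children during the time it is concurrently conducted with the ITIP1 and ITIP2 clinical trials". For the comparators, "We also assume that 1000 children can be enrolled in each of the standard care groups in ITIP1 and ITIP2". Expected outcomes are that "clinical cure will be observed in 90%-95% of children in ITIP1 and 85%-90% in ITIP2". Table 1 then lists, for comorbidity subgroups of 40 to 200 children, the absolute difference that can be seen against 1000 comparators with cure of 95%, 90% or 85%. Its footnote reads "Alpha value set to 5% and power set to 80" (percent). In the worked example, 100 children with HIV infection or exposure are set against the ITIP2 standard care group: "we will have 80% power to detect an absolute difference in proportions of 9.9" percentage points, that is 90% against 80.1%.

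The Statistical Analysis section names the method for these same comparisons: "Generalized linear models with robust standard error will be used to compare the percentages (absolute risk differences" being the effect measure, and "Two-sided tests will be performed, with an alpha value of 0.05". The article names no formula for Table 1. It also does not state the link function, the test statistic (Wald or score) or whether the primary comparison is unadjusted.

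**The concern.** With one binary exposure and no covariates, the robust variance of a risk difference is the unpooled two-sample variance. Most sample-size formulas for two proportions set the critical value with a pooled variance. The two nearly agree when the groups are of similar size. Here they do not: 1000 children face 40 to 200, and the small group has the lower cure rate and so the larger variance. Pooling with 1000 comparators hides most of that variance.

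At stake is how a non-significant result is read. In the small HIV or malnutrition subgroups it could be taken as coming from a comparison with 80% power when the test actually used had far less. The study asks whether cure is lower in children with comorbidities, and that is the direction in which the robust Wald test is conservative.

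**Working it through.** **Inputs** (Sample Size, Table 1, Statistical Analysis): comparator n1 = 1000; subgroup n2 = 40 to 200; comparator cure p1 = 0.95, 0.90 or 0.85; subgroup cure p2 = p1 minus the printed difference d; two-sided alpha 0.05; full subgroup sizes, with no loss to follow-up. The 24 rows contain 21 distinct combinations. Two entries needed a reading. The anemia difference that prints without its decimal is taken as 11.4 (85 − 73.6). The HIV row with n2 = 50 and 90% comparator cure prints 81.3%, but 90 − 13.9 = 76.1, so the stated difference is used.

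**Formulas**
- Pooled: SE0 = √[p̄(1−p̄)(1/n1 + 1/n2)], where p̄ is the overall cure proportion.
- Unpooled (robust): SE1 = √[p1(1−p1)/n1 + p2(1−p2)/n2].
- Power of the pooled test ≈ Φ[(d − 1.96·SE0)/SE1].
- Power of the robust Wald test ≈ Φ[d/SE1 − 1.96].

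**Step 1: reproduce the worked example.** p̄ = (900 + 80.1)/1100 = 0.891. SE0 = √(0.891 × 0.109 × 0.011) = 0.0327. SE1 = √(0.00009 + 0.001594) = 0.0410. Pooled power = Φ[(0.099 − 0.0641)/0.0410] = Φ(0.85) = 80.3%. The plan's figure is recovered.

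**Step 2: reproduce the table.** The pooled formula gives 79.6% to 80.3% in every combination. Solved for 80% power, it returns the printed differences to within 0.1 point, for example 5.50, 7.17 and 8.31 (n2 = 200), 9.86 (n2 = 100, 90%), and 12.25, 15.59 and 17.81 (n2 = 40). The alternatives do not give 80% across the table: continuity-corrected 73% to 77%, arcsine 71% to 78%, one-sided unpooled 65% to 83%, two-sided unpooled 53% to 74%.

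**Step 3: robust Wald test at the same differences.** For the worked example, the normal approximation gives Φ(0.099/0.0410 − 1.96) = Φ(0.45) = 67.5%. Exact enumeration of both binomials gives 69.7%. Exact power for the whole table:

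| Subgroup n | Comparator 95% | 90% | 85% |
|---|---|---|---|
| 200 | 70.8% | 73.9% | 75.1% |
| 150 | 68.3% | 71.4% | 73.8% |
| 100 | 62.9% | 69.7% | 72.5% |
| 75 | 60.2% | 66.7% | 70.3% |
| 70 | 59.2% | 66.3% | 70.6% |
| 50 | 55.6% | 63.9% | 68.5% |
| 40 | 52.4% | 62.4% | 67.6% |

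The same enumeration gives the pooled score test 79.6% to 81.1%. A small-sample correction to the robust SE (HC1) changes the Wald figures by less than one point.

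**Step 4: behaviour under no effect.** The robust Wald test rejects for lower cure in 0.3% to 1.8% of cases and for higher cure in 3.6% to 12.9%, each against a nominal 2.5%; the total is 5.4% to 13.2%. The extreme is easy to see. With n2 = 40 and 95% cure, all 40 children are cured with probability 0.95^40 = 12.9%. The subgroup then contributes no variance and the test declares higher cure. The pooled score test stays at or below 5% in total, but rejects for lower cure in 2.8% to 3.9% of cases.

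**Step 5: differences giving the robust Wald test 80% power.**

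| Case | Printed | Exact | Normal approximation |
|---|---|---|---|
| n = 100, 90% (worked example) | 9.9 | about 11.3 | 11.9 |
| n = 200, 95% | 5.5 | about 6.2 | 6.6 |
| n = 40, 95% | 12.2 | about 17.2 | 19.0 |
| n = 40, 85% | 17.8 | about 20.8 | 21.6 |

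**The case against.** A reader might infer that the planned analysis simply has 52% to 75% power. The article does not support that. It names a generalized linear model, a robust standard error and a risk-difference effect measure, but neither the link nor the test statistic. If the exposure coefficient of a logistic model is tested by Wald and the risk difference is only reported, exact power at the printed differences is 77.9% to 80.0%, and Table 1 stands almost unchanged. If the standardised risk difference is itself tested by the delta method, the lower figures return. Testing the risk difference directly is the natural reading, but it remains a reading. The full protocol in Multimedia Appendix 1, not at hand, may settle it.

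Nor does the article say that the primary comparison is unadjusted. Its Limitations and Bias section expects adjustment for baseline characteristics where possible, and the cohorts differ in eligibility, treatment and follow-up schedule. For an adjusted model, neither 80% nor 52% to 75% is the power.

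A reader might also conclude that the study is too small and must be enlarged. That does not follow either: the 1000 children come from what could be enrolled alongside the two trials, and the detectable differences were worked out afterwards. The study is also described as exploratory, although the article uses that only to waive a multiplicity adjustment and lists the comparison among the primary objectives.

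Lastly, the pooled score test is not a flawless substitute. It is mildly liberal in the direction of interest, and part of its 80% power comes from that.

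What stands is that a stated power and a stated analysis do not match on the natural reading, and that the article does not say for which test the 80% holds.

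**Conclusion.** The concern holds in conditional form. The 80% in Table 1 and the worked example belongs to a pooled two-proportion test. That is an inference, since no formula is named, but it rests on agreement in all 21 combinations. If the unadjusted risk difference is tested by its robust Wald statistic, no row reaches 80%. The shortfall is about 5 points at best (n = 200, 85%) and about 28 at worst (n = 40, 95%), and the null tails are unbalanced.

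These figures assume no covariates, full subgroup sizes and the comparator cure rates in Table 1. Any loss to follow-up would lower power further. The estimates of cure and of the risk differences are unaffected. Because no sample size or decision rests on the 80%, this is a should-fix.

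**What to change.** Choose one of two routes and state it.

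- **(a) Keep the robust risk-difference test and restate Table 1 and the worked example for it.** The Step 5 exact values show the size of the change; the remaining rows should be solved the same way, naming the method (exact or normal approximation), since the two differ by up to about 2 points.
- **(b) Keep the risk difference as the reported effect, but base the unadjusted hypothesis test on a score test with score intervals (Miettinen–Nurminen), or on the logit coefficient.** Table 1 then holds approximately. Add a note that the pooled score test rejects for lower cure in 2.8% to 3.9% of null cases against a nominal 2.5%.

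On either route, keep the robust-SE model for the covariate-adjusted comparison, state the link and test statistic, and say that Table 1 refers to the unadjusted comparison. When restating, reconcile the HIV row that prints a 13.9-point difference from 90% beside 81.3%.

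The cost is a recalculated table for (a), or a sentence or two in the analysis section for (b). Neither needs more children or more data.

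### At Table 1's group sizes the planned robust-standard-error test of the risk difference has a type I error of 5.4%–13.2%, not 5%, and power of 52%–75%, not 80%

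*Protocol article*

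**What the plan says.** The Statistical Analysis section fixes the primary method: "Generalized linear models with robust standard error will be used to compare the percentages (absolute risk differences) of children who are clinically cured". The time point is day 14, and the comparison is made separately for severe malaria, anemia, severe acute malnutrition and HIV infection or exposure, each against standard care in ITIP1 or ITIP2. It adds: "Two-sided tests will be performed, with an alpha value of 0.05". There is no multiplicity adjustment, so each test carries its own 5%.

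The Sample Size section sets the conditions. On ITIP3: "We estimate that the study can enroll 1000 children during the time it is concurrently conducted with the ITIP1 and ITIP2 clinical trials". On the comparators: "We also assume that 1000 children can be enrolled in each of the standard care groups in ITIP1 and ITIP2". On cure: "we conservatively estimate that clinical cure will be observed in 90%-95% of children in ITIP1 and 85%-90% in ITIP2". Table 1 turns the assumed prevalences into groups of 150–200 (severe malaria), 75–100 (anemia), 50–100 (HIV) and 40–70 (severe acute malnutrition). It lists the difference detectable in each with 80% power at 5% alpha. The stated question is whether cure is lower with the comorbidity.

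**The concern.** In a two-group model, the robust variance of the risk difference takes each group's contribution from that group's own observed cure rate. In a group of 40–100 with cure near 85%–95%, only a few children are not cured. A sample that by chance has fewer non-cures also gets a smaller estimated variance, and with none its contribution is zero. A sample with more non-cures gets a larger variance. The test therefore rejects too readily when the comorbidity group happens to look better and too rarely when it looks worse.

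Two stated operating characteristics are at stake: the 5% level of the primary tests, and the 80% power in Table 1 for finding lower cure.

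**Working it through.** **Inputs.** Comparator n0 = 1000; comorbidity group n1 = 40, 50, 70, 75, 100, 150 or 200; comparator cure 95%, 90% or 85%; two-sided 0.05. All come from the Sample Size section, Table 1 and the Statistical Analysis section. Anemia and HIV share the n = 100 rows, so there are 7 × 3 = 21 distinct scenarios. Alternatives are comparator cure minus the listed difference. In three rows the printed entries needed reading: HIV 5% at 90% cure (90 − 13.9 = 76.1 was used, not the printed 81.3), anemia 7.5% at 85% (85 − 13.1 = 71.9, printed 72.0), and anemia 10% at 85% (difference incomplete; 85 − 73.6 = 11.4).

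**Step 1: reproduce the plan's figure.** Worked example: 100 against 1000, 80.1% against 90%.

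- Pooled proportion: (80.1 + 900)/1100 = 0.891.
- Null SE: √[0.891 × 0.109 × (1/100 + 1/1000)] = 0.0327.
- Alternative SE: √[0.801 × 0.199/100 + 0.9 × 0.1/1000] = 0.0410.
- Pooled-variance power: Φ[(0.099 − 1.96 × 0.0327)/0.0410] = Φ(0.85) = 80%.
- Unpooled power, the form the robust test uses: Φ(0.099/0.0410 − 1.96) = Φ(0.45) = 67%.

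Across all 21 scenarios the pooled formula gives 79.6%–80.3% and the unpooled formula 53%–74%. Table 1 therefore rests on a pooled-variance test.

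**Step 2: exact behaviour of the planned test.** With one binary group term, z = (p1 − p0)/√[p1(1 − p1)/n1 + p0(1 − p0)/n0], rejecting if |z| > 1.96. Every outcome was enumerated over Binomial(n1) × Binomial(1000), with equal cure for the error rate and Table 1's difference for power. Cells show type I error % (false 'lower cure' tail %, nominal 2.5) / power %.

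| n1 | 95% cure | 90% cure | 85% cure |
|---|---|---|---|
| 40 | 13.2 (0.3) / 52.4 | 9.0 (0.8) / 62.4 | 7.6 (1.2) / 67.6 |
| 50 | 9.2 (0.4) / 55.7 | 8.9 (0.9) / 63.9 | 7.2 (1.2) / 68.5 |
| 70 | 11.4 (0.6) / 59.2 | 7.4 (1.0) / 66.3 | 6.5 (1.4) / 70.6 |
| 75 | 10.2 (0.6) / 60.2 | 7.3 (1.0) / 66.8 | 6.4 (1.4) / 71.0 |
| 100 | 8.3 (0.7) / 62.9 | 6.6 (1.2) / 69.7 | 6.0 (1.5) / 72.5 |
| 150 | 7.0 (1.1) / 68.3 | 5.9 (1.4) / 71.4 | 5.6 (1.7) / 73.8 |
| 200 | 6.3 (1.2) / 70.8 | 5.5 (1.6) / 73.9 | 5.4 (1.8) / 75.2 |

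The share of errors that falsely show higher cure is 12.86/13.19 = 97% at n = 40 and 95% cure, 79%–97% for n = 40–75, and 67% at n = 200 and 85% cure. Other robust variants barely change the worst cell: HC1 13.2%, HC2 13.2%, HC3 13.1%.

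**Step 3: the extreme sample.** Suppose 40/40 are cured against 950/1000.

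- Robust: SE = √(0.95 × 0.05/1000) = 0.0069, all from the comparator. The 95% interval is +3.6 to +6.4 points, p = 4 × 10⁻¹³.
- Bootstrap around a Firth fit: +2.5 to +5.2 points, still excluding zero, because every resample of the group is again fully cured.
- Newcombe: −3.8 to +6.5 points.
- Score test: pooled cure 990/1040 = 0.952; z = 0.05/√[0.952 × 0.048 × (1/40 + 1/1000)] = 1.45, not significant.
- Firth penalised likelihood ratio. Free maximum: 950.5 ln(950.5/1001) + 50.5 ln(50.5/1001) + 40.5 ln(40.5/41) + 0.5 ln(0.5/41) = −202.74. Equal cure: 991 ln(991/1042) + 51 ln(51/1042) = −203.60. Twice the difference is 1.73 on 1 df, p = 0.19.

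**Step 4: the alternative on the same enumeration.** The pooled score test has type I error 3.8%–5.0% and power 79.6%–81.1% over all 21 scenarios. Newcombe gives essentially the same. Neither splits its tails evenly: the score test's 'lower cure' tail is 2.8%–3.9%, so it is mildly liberal there while the two-sided total stays at about 5% or below.

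**The case against.** The strongest reply is that the headline figure is a corner case. The 13.2% needs the lowest prevalence (4%, n = 40) together with the highest cure rate (95%). Almost all of it comes from samples with every child cured (probability 12.9%), which any analyst would notice. This stands as a limit on size. It does not remove the problem: with such samples set aside, n = 70 at 95% cure is still 8.6% and n = 50 at 90% is still 8.4%.

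Second, the inflation needs near-equal cure, which is doubtful for these children. If true cure is 5 points lower, false 'higher cure' falls to 1.2%–1.5% at n = 40 and 0.1%–0.2% at n = 100. This also stands. But in exactly that situation the other consequence applies, namely the loss of power to show lower cure.

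Third, the group sizes are soft. Every enrolled child must have a qualifying condition, yet the upper planning prevalences sum to only 24 + 20 + 7 + 10 + 10 = 71%, so some groups must exceed plan. Which ones is unknown, and every scenario up to n = 200 exceeds 5%.

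Fourth, the article names no family, link or sparse-data rule, and a full protocol or SAP may do so. That is fair, but the article does name the variance estimator and the level, and those are what conflict. The exploratory label explains the absence of multiplicity adjustment. It does not make each test's 5% true.

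**Conclusion.** The concern holds in limited form. The stated test does not keep its 5% level in any of the 21 Table 1 scenarios (5.4%–13.2%; at most 9.0% at the ITIP2 cure rates). Its power at Table 1's differences is about 52%–75%, not 80%. For the study's own question, the power loss is the more important consequence.

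A reader might infer that the primary analysis as a whole has a 13% false-positive rate, nearly all of it pointing to better cure. The documents do not support that: it describes one cell, and at n = 150–200 the rate is 5.4%–7.0%. Nor is a false claim of lower cure made more likely; it is rarer than nominal. Nor is the 80% in Table 1 a miscalculation; it is right for a pooled-variance test, which is not the test the analysis section names.

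The result assumes a Wald test without covariates, 1000 comparators per trial and no loss to follow-up. It should be fixed, mainly for the severe acute malnutrition, HIV and anemia contrasts; severe malaria is affected least.

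**What to change.** In the Statistical Analysis section, specify a score-type test and interval (Miettinen-Nurminen or Newcombe) for the primary unadjusted risk differences. This brings the analysis into line with the pooled-variance basis of Table 1.

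For adjusted contrasts in groups with few or no non-cures, specify a penalised-likelihood (Firth) model with profile-likelihood inference. Do not rely on a bootstrap or on any of HC0–HC3, since all of these collapse when every child in the group is cured.

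The cost is a change of wording, with standard methods and no new data. The downside is slightly wider intervals in the smallest groups.

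### Table 1 sets each whole ITIP3 comorbidity group, both pneumonia types together, against a single-type trial, and the analysis does not say whether comparisons are matched by type

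*Protocol article*

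**What the plan says.** ITIP3 enrolls children with fast breathing or chest indrawing pneumonia (Study Participants). Each concurrent trial covers one type: ITIP1 fast breathing, ITIP2 chest indrawing (Introduction; Table 1 footnotes b and d).

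Under Statistical Analysis, ITIP3 children with severe malaria, anemia or severe acute malnutrition, "or are HIV positive or exposed) and children in the standard care groups in ITIP1 or ITIP2", are compared on day-14 cure as absolute risk differences. "Two-sided tests will be performed, with an alpha value of 0.05". No restriction or stratification by pneumonia type is stated.

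The Sample Size section gives the planning inputs:

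- ITIP3 size: "We estimate that the study can enroll 1000 children during the time it is concurrently conducted with the ITIP1 and ITIP2 clinical trials".
- Comparator size: "We also assume that 1000 children can be enrolled in each of the standard care groups in ITIP1 and ITIP2".
- Cure by trial: "we conservatively estimate that clinical cure will be observed in 90%-95% of children in ITIP1 and 85%-90% in ITIP2".

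Table 1 then lists detectable differences at 80% power, with N equal to prevalence × 1000 (for example 20% gives 200). The worked example sets an HIV group of 10% of ITIP3, that is 100 children, against ITIP2 and quotes 9.9 points. Footnote e, attached to the N column, reads "Assuming similar values for fast breathing pneumonia and chest indrawing pneumonia to be able to compare the ITIP1 and ITIP2 cohorts".

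**The concern.** The N in Table 1 is the full comorbidity group, and the same N serves the 95% rows, which under the stated ranges only ITIP1 can reach, and the 85% rows, which only ITIP2 can reach. Two analyses are compatible with the text, and each has a problem.

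- **Matched by type.** Fast breathing children go against ITIP1 and chest indrawing children against ITIP2. Each comparison then has only part of the group, so the table overstates power.
- **Not matched.** A mixed group is set against a trial of one type. Any difference in cure between types then appears as a comorbidity effect against ITIP1, and hides one against ITIP2.

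This comparison is one of the two stated primary objectives and the one used for hypothesis testing. At stake is either the power claim or the meaning of the risk difference.

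**Working it through.** **Inputs from the article.** Two-sided alpha 0.05; power 80%; n1 = 1000 in each standard care group; ITIP3 total 1000; cure 90%–95% (ITIP1) and 85%–90% (ITIP2). **Not given:** the type split within ITIP3. I assume 50/50 and show 30% and 70%.

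**Step 1: reproduce Table 1.** Pooled two-proportion normal approximation:

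- p̄ = (n1·p1 + n2·p2)/(n1 + n2)
- SE0 = √[p̄(1 − p̄)(1/n1 + 1/n2)]
- SE1 = √[p1(1 − p1)/n1 + p2(1 − p2)/n2]
- power = Φ[(|p1 − p2| − 1.96·SE0)/SE1]

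Worked example (p1 = 0.90, p2 = 0.801, n2 = 100): p̄ = 0.891, SE0 = 0.0327, SE1 = 0.0410, power = Φ[(0.099 − 0.0641)/0.0410] = Φ(0.85) = 80%. Solving for exactly 80% gives 9.86 points; the article prints 9.9. The formula matches all 21 distinct combinations of N and cure rate in Table 1 to within 0.05 point, reading the anemia cell printed as 11.% as the 11.4 shown in the identical HIV row. For the worked example, one-sided (8.73), unpooled (11.88) and continuity-corrected (10.46) versions do not match. So each printed difference needs the whole comorbidity group in one comparison.

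**Step 2: matched reading, 50/50 split.** Same example with n2 = 50: p̄ = 0.895, SE0 = 0.0444, SE1 = 0.0573, power = Φ[(0.099 − 0.0870)/0.0573] = Φ(0.21) = 58%.

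| Whole-group N | Comparator cure | Printed difference | Difference at half N | Power at printed difference, half N |
|---|---|---|---|---|
| 200 | 95% | 5.5 | 7.6 | 60% |
| 200 | 90% | 7.2 | 9.9 | 59% |
| 100 | 90% | 9.9 | 13.9 | 58% |
| 70 | 90% | 11.7 | 16.7 | 58% |
| 40 | 90% | 15.6 | 22.4 | 59% |
| 40 | 85% | 17.8 | 25.3 | 57% |

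Over all combinations, power at the printed difference is 57%–61%. For a type holding 30% of the group it is about 42%–49%; for a type holding 70%, about 68%–70%. Supplying the printed N to both comparisons at 50/50 would need about 2 × 1000 = 2000 ITIP3 children.

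**Step 3: unmatched reading, no comorbidity effect.** Expected cure in the group = c × (chest indrawing cure) + (1 − c) × (fast breathing cure), where c is the chest indrawing share. The planning ranges allow a type gap from 90 − 90 = 0 to 95 − 85 = 10 points.

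- Gap 0 (both 90%): bias 0.
- Gap 5, c = 0.5: at 95%/90% the group is expected at 92.5%, and at 90%/85% at 87.5%. Either way the bias is a 2.5-point deficit against ITIP1 and a 2.5-point surplus against ITIP2. Rejection against ITIP1 (the formula above, both tails) is 20% (90/85) to 32% (95/90) at n2 = 200, and 14.5% to 22.8% at n2 = 100, against a nominal 5%.
- Gap 5, c = 0.3: the bias is 1.5 points against ITIP1 and 3.5 points the other way against ITIP2.
- Gap 10, c = 0.5: 5.0 points each way; rejection against ITIP1 is 74% at n2 = 200 and 54% at n2 = 100.

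**The case against.** **The article does not say that groups are pooled.** This stands. The Statistical Analysis section is silent on type, the objective names the two types separately, and the full protocol in Multimedia Appendix 1 is not shown. A reader might infer that the analysis is certainly confounded, with false rejection as high as 67%. The documents do not support that: 67% needs an unmatched analysis, cure of 95%/90%, a 90% chest indrawing share and N = 200 all together. If the analysis is matched, however, Table 1 is what fails, and the article prints Table 1.

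**Footnote e deals with it.** It does not. If similar values means the same N for each type, 1000 children cannot supply it. If it means similar cure, it agrees with "clinical cure will be observed in 90%-95% of children in ITIP1 and 85%-90% in ITIP2" only at the shared value of 90%.

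**Pneumonia type is missing from the covariate list.** This is weak evidence of pooling. The list follows the sentence on secondary outcomes and contains HIV status and malaria, which are themselves exposures of interest. Limitations and Bias also promises adjustment for baseline characteristics where possible, without naming or excluding type. But adjustment cannot repair a contrast with ITIP1 alone if that trial has no chest indrawing children.

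**A child with both signs meets both definitions in Textbox 1.** True as worded, but counting that child in both comparisons brings back the mixing of types.

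**Enrollment is feasibility-driven, the study is called exploratory, and much of the halved grid is already printed.** Partly right. Halving 200, 150 or 100 gives 100, 75 or 50, all in Table 1, and the authors regard every tabulated effect as clinically relevant. Halved malnutrition groups (35 or 20), HIV at 5% (25) and, marginally, anemia at 7.5% (37 or 38) fall outside the grid: 25.3 points compares with a largest printed value of 17.8.

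**Conclusion.** The point holds. Table 1 and the worked example use the whole mixed-type comorbidity group as N against a single-type trial, and the analysis text does not say whether comparisons are matched. No reading keeps both the printed power and an unconfounded contrast, unless both types cure at the same rate.

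On the matched reading, which the objective favors, power is 57%–61% at an assumed 50/50 split instead of 80%, and lower for whichever type is scarcer. On the unmatched reading, bias ranges from zero to several points, depending on a type gap that the article leaves anywhere from 0 to 10 points and a type split that it does not give. It would be too strong to say that the plan expects a gap of about 5 points; that is one value inside its ranges.

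**What to change.** 1. State in Statistical Analysis that ITIP3 children with fast breathing only are compared with the ITIP1 standard care group, and those with chest indrawing (with or without fast breathing) with the ITIP2 standard care group, so that each child enters one comparison.
2. Restate Table 1 and the worked example with type-specific N over a range of type splits, such as 30%, 50% and 70%, and reword footnote e to say what is assumed.
3. Where one estimate per comorbidity is wanted, combine the two type-specific risk differences by stratification, which uses every child once.

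The cost is wording and a recomputed table. Type is part of the enrollment case definition, so no new data are needed. The downside is larger detectable differences and wider type-specific intervals; the combined estimate recovers precision but is a weighted average if the effect differs by type. Matching does not remove the other differences in eligibility, treatment and follow-up that Limitations and Bias already acknowledges.
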